## Abstract

**Background:**

Support groups for children in troubled families are available in a majority of Swedish municipalities. They are used as a preventive effort for children in families with different parental problems such as addiction to alcohol/other drugs, mental illness, domestic violence, divorce situations, or even imprisonment. Children from families with these problems are a well-known at-risk group for various mental health and social problems. Support groups aim at strengthening children’s coping behaviour, to improve their mental health and to prevent a negative psycho-social development. To date, evaluations using a control-group study design are scarce. The aim of the current study is to evaluate the effects of support groups. This paper describes the design of an effectiveness study, initially intended as a randomized controlled trial, but instead is pursued as a quasi-experimental study using a non-randomized control group.

**Methods/design:**

The aim is to include 116 children, aged 7–13 years and one parent/another closely related adult, in the study. Participants are recruited *via* existing support groups in the Stockholm county district and are allocated either into an intervention group or a waiting list control group, representing care as usual. The assessment consists of questionnaires that are to be filled in at baseline and at four months following the baseline. Additionally, the intervention group completes a 12-month follow-up. The outcomes include the Strength and Difficulties Questionnaire (SDQ S11-16), the Kids Coping Scale, the “Ladder of life” which measures overall life satisfaction, and “Jag tycker jag är” (I think I am) which measures self-perception and self-esteem. The parents complete the SDQ P4-16 (parent-report version) and the Swedish scale “Familjeklimat” (Family Climate), which measures the emotional climate in the family.

**Discussion:**

There is a need for evaluating the effects of support groups targeted to children from troubled families. This quasi-experimental study therefore makes an important contribution to this novel field of research. In the article various problems related to pursuing a study with children at risk are discussed.

**Trial registration:**

ISRCTN52310507

## Background

Children who grow up in families with parental problems like for instance mental health or substance abuse problems, run an increased risk of developing a number of different physical and psychological health issues, as well as social problems (*e.g.*, [1-6]). Available figures indicate that this is widespread, affecting many children who experience one or more of these problems in their families. For instance, international estimates indicate that 12-39% of all children have parents with mental health problems [7-10]; 10-40% are affected by domestic violence [11-13]; 8-30% grow up with at least one problem drinking parent [14-17]; about 2% of US children have a parent in prison [18]. In Sweden, figures are similar, revealing that about 6% of all children aged 0–17 have at least one parent who has received inpatient psychiatric care [19], and approximately 20% have parents with alcohol problems [20,21], while about 30% of all children have divorced parents (http://www.scb.se) and approximately 2% have a parent in prison [22].

Support is available to these children *via* for instance the Child and Adolescent Psychiatric Care (BUP), the general school health care and the Social Services, who provide support through Family Centres (Familjecentraler), Contact Families (where children can spend weekends) [23] and in severe cases, foster care. Additionally, a relatively novel way to offer intervention programs to this target group is by the use of the Internet and there are currently a small number of internet-based controlled trials ongoing [24,25]. The most commonly offered intervention in Sweden to children in troubled families is support groups run by the Social Services and/or NGOs. Regardless of the underlying problem within the family, these support group interventions are all derived from the same fundamental psycho-educative manual-based intervention called Children are People Too (CAP) [26-28]. The support group interventions are aimed at strengthening children’s feeling of self-worth, their competencies and coping behaviour, and thereby to prevent a negative psycho-social development. Briefly, the groups provide information about the parent’s problems and children are able to share their experiences with other children during 8–15 weekly one and a half hour long meetings each addressing a special theme.

There are only a few estimates available reporting on the number of existing support groups in Sweden. Moreover, figures on how many children there are who attend support groups every year are even scarcer. According to a survey from 2009 by the Swedish National Institute of Public Health [29], support groups for children in families with parental substance abuse problems were available in 90% of all municipalities. For children affected by parental mental illness, the same figure was 73%, for children who have witnessed domestic violence the figure was 64% and 38% for children having a parent in prison. More recent surveys made by the Swedish Save the Children and the junior association of the Swedish IOGT-NTO (Junis) also show that the vast majority of municipalities provide support groups to children experiencing parental problems [30,31]. Yet, despite the fact that most municipalities do provide resources for support, only a small proportion of all children who live in troubled families attend this support. For instance, in an annual survey by Junis figures reveal that only 1-2% of all children who have parents with substance abuse problems attend support groups [31].

To our knowledge there are few controlled trials reported in the literature, measuring the effects of support groups with a theoretical basis in CAP. However, a few studies have been conducted using a quantitative approach, but without a control group. For instance, a Swedish effect study of 300 children aged 7–22 [26] was pursued without a control group, but using added value as the method of analyses [32,33]. Results revealed an improvement among the participants with regards to their mental health status, overall life satisfaction and hopefulness [26]. Results from another study using a small group of children who had attended a CAP-based support group after experiencing family violence, indicated an improved mental health status among the participating children [34]. Nonetheless, there is still a lack of evidence for CAP-based support groups and we have therefore designed a quasi-experimental controlled trial which evaluates the effectiveness of support group interventions targeted to children experiencing a wide variety of parental problems. Our hypothesis is that these support groups will render in positive effects among 7–13 year olds.

### Objective and research questions

The objective of this study is to evaluate the effectiveness of support groups provided to children who grow up in families with parental problems (*i.e.,* addiction to alcohol and/or other drugs, mental illness, domestic violence, divorce situation or imprisonment). Specific research questions concerns the children’s improvement in mental health, coping behaviour and quality of life, which includes overall life satisfaction and future hope, self-perception and self-esteem, and emotional climate and personal interaction.

## Methods/design

This study was originally designed as a two-armed randomized controlled trial (RCT). However, after several months of unsuccessful recruitment efforts, the randomization protocol was abandoned and the study redesigned as a quasi-experimental control group study (Figure 1). The reason for abandoning the RCT-design was the unwillingness of support group therapists to randomize participants into the control condition. This was due to the fact that support group therapists did not consider it ethically sound to randomly allocate children, who actively had sought support (by themselves or by their parents), into the control condition.

**Figure 1 F1:**
[figure not shown]
Flow chart diagram representing the design of the study.

### The target sample

The aim is to include at least 116 children, aged between 7 and 13 years at the point of enrolment, who intend and are eligible to participate in existing support group interventions targeted to children who grow up and live in families with at least one of the following parental problems: (1) addiction to alcohol and/or other drugs, (2) mental illness, (3) domestic violence, (4) divorce situation or (5) imprisonment. Participants will be excluded from the study if they do not meet the inclusion criteria, if they previously have participated in a support group intervention, or if they (or their parents) do not consent to participate.

### Recruitment

Recruitment has been ongoing since March 2010 *via* schools, the social services and various existing support groups for children having parents with any of the above mentioned problems. Additionally, there has been advertisments in free newspapers (Metro) which is locally distributed in the Stockholm and Uppsala region and the local newspaper in Stockholm (Mitt i). The catchment area of the study is the Stockholm county district, although a support group located in the Uppsala Region has been contacted and asked to contribute to the recruitment.

Staff at schools, adult mental health clinics and social services, along with support group therapists have been informed about the study and instructed on how to inform both children and their parent(s) about the study. To facilitate this work, pamphlets describing the study have been provided to those concerned. To participate in the study, parents or support group therapists need to visit a website which has been created specifically for this study (http://www.barngruppstudien.se), and apply for enrolment. Once signed up, the project manager sends out further information and a written informed consent to the parents/custodians and to the child, to be sent back to the project manager using a prepaid reply envelope. For the child to be included in the study, the written informed consent has to be signed by at least one parent/custodian. If only one parent signs the consent form, a passive parental consent procedure is adopted, which means that the other parent is informed and reminded of his/her right to say no.

### Assessment

Before being allocated to one of the two study conditions, participants have to complete the baseline measurement. All study participants also have to complete a follow-up assessment four months after the initial measurement. Additionally, the intervention group participants have to complete a second follow-up assessment 12 months after the initial measurement. This 12 month follow-up will only be available for the intervention group participants as the control group participants, for ethical reasons, will be offered the intervention after the four-month follow-up. All measurements are performed using paper-based questionnaires. The participants in the intervention group complete the initial baseline assessment during the first individual meeting, which precedes the first support group meeting. Baseline data from the interventions group is collected by the support group therapist responsible for the individual meeting, or by the project staff. Data from the four month follow-up assessments are collected by the project staff. For the 12 month follow-up (intervention group only), questionnaires are either distributed by regular mail (with telephone support available if needed) or in a meeting with the project staff (if requested by the child/parent). Data from the control group participants will be distributed and collected by the project staff in person or by using regular mail with telephone support if necessary. As a compensation for completing each assessment, children and parents are each given a gift card corresponding to approximately 22 or 11 Euro, respectively.

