### Allocation

After completing the baseline assessment, participants are allocated to the intervention or the control group which represents care as usual (CAU). Due to the aforementioned reasons for abandoning the original randomization protocol, the vast majority of the control group participants are recruited from the support groups’ own waiting lists. Participants were informed about their group belonging by the project manager.

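### Some intervention-arm baselines may be collected by a support group therapist, while control forms and all four-month forms go through project staff, so a collector effect can enter one arm's self-reported baseline

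*Protocol article*

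**What the plan says.** The Assessment section of the protocol article sets out collection by arm and time point.

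- **Intervention, baseline, setting:** "The participants in the intervention group complete the initial baseline assessment during the first individual meeting, which precedes the first support group meeting".
- **Intervention, baseline, collector:** "Baseline data from the interventions group is collected by the support group therapist responsible for the individual meeting, or by the project staff".
- **Control:** "Data from the control group participants will be distributed and collected by the project staff in person or by using regular mail with telephone support" where needed. No therapist is named.
- **Four months:** "Data from the four month follow-up assessments are collected by the project staff". The sentence gives no mode.
- **12 months, intervention only:** "questionnaires are either distributed by regular mail (with telephone support available if needed) or in a meeting with the project staff", the meeting being on request.

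All forms are on paper. Under Primary outcomes, every scale is answered by the child or by a parent. Under Analyses, the main comparisons are of means between and within groups at baseline and follow-up; collector and mode are not mentioned. Strengths and limitations names selection bias, mixed family problems, lack of stratification and short follow-up, but not the way the forms are collected.

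**The concern.** Children aged 7–13 and their parents report on mental health, self-esteem, coping and family climate, in families with problems such as addiction or violence. Such answers may depend on who receives the form. A family may stress its problems to someone from the service it hopes to use, or play them down. If a therapist receives some baselines in one arm and project staff receive everything else, that dependence appears as an arm difference at baseline and as change over time in the intervention arm. Without a record of who collected each form, the analysis cannot tell this apart from an effect of the groups. The 12-month evidence is within-group only, so no control change can offset it there.

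**Working it through.** **1. Collection by arm and time (Assessment section)**

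| | Baseline | 4 months | 12 months |
|---|---|---|---|
| Intervention, collector | therapist or project staff | project staff | mail, or meeting with project staff |
| Intervention, mode | at an individual meeting | not stated | mail or meeting |
| Control, collector | project staff | project staff | none planned |
| Control, mode | in person or mail | in person or mail | none planned |

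The collector can differ between arms only at baseline. It changes over time only for intervention children whose baseline a therapist took. Mode is not held constant in either arm.

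**2. Where a baseline shift goes**

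Let therapists take a share *s* of intervention baselines, and let each such form shift by *b* SD. The intervention baseline mean then moves by *s·b*. The resulting bias is:

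- baseline comparison of the arms: *s·b*
- within-group change at 4 or 12 months, and between-group difference in change: *s·b* in absolute size
- four-month comparison adjusted for baseline: *s·b* times the baseline slope
- direct comparison of four-month means: 0

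**3. The plan's own sample size**

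Inputs from the Sample size section: d = 0.5, ratio 1.8, one-sided α = 0.05, power 0.80, stated result 75 + 41 = 116. A t-test needs 71 + 39 = 110. A Wilcoxon-Mann-Whitney calculation (relative efficiency 3/π) needs 74 + 41 = 115. At 75/41, power is 0.820 by t-test and 0.804 by Wilcoxon-Mann-Whitney. The stated size is consistent with its inputs, and 75/41 can be used below.

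**4. Illustration: difference-in-change test, no true effect**

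The documents give neither *s* nor *b*, so both are assumed. The change score is taken to have the same SD as the outcome. Since Var(change) = 2(1 − ρ)σ², this means a baseline to follow-up correlation of ρ = 0.5, also an assumption.

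- Degrees of freedom: 75 + 41 − 2 = 114; critical t = 1.658.
- Noncentrality = *s·b* × √(75 × 41 / 116) = *s·b* × 5.149.
- False-positive rate = P(noncentral t > 1.658).

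| Shift *b*, favouring intervention | *s* = 25% | *s* = 50% | *s* = 100% |
|---|---|---|---|
| 0.1 SD | 6.5% | 8.2% | 12.9% |
| 0.2 SD | 8.2% | 12.9% | 26.7% |
| 0.3 SD | 10.4% | 19.0% | 45.6% |

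For example, *b* = 0.2 and *s* = 50% give *s·b* = 0.10, noncentrality 0.515 and a rate of 12.9% against the nominal 5%.

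**5. The same shift in the other direction, true d = 0.5**

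The effective difference is 0.5 − *s·b*. Power falls from 0.82 to 0.74, 0.66 and 0.56 at *s* = 50%, and to 0.66, 0.46 and 0.27 at *s* = 100%, for *b* = 0.1, 0.2 and 0.3.

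**The case against.** The strongest reply is that the main controlled result need not be affected. Project staff collect in both arms at four months, and the Analyses section compares means without specifying a between-group change score. A direct four-month comparison is free of the baseline shift, and adjustment for baseline lets in only part of it. This stands. It limits the point to the analyses that use baseline, which the section also plans.

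Several stronger readings are tempting but not supported:

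- *Collector and mode are tied to arm and change only in the intervention arm.* The text allows project staff at intervention baselines too, and control children may move between mail and in-person completion.
- *The collector is the child's own future group leader, who helps or sees the answers.* The article says only that the therapist responsible for the individual meeting collects the forms. Instructions on privacy may be in the full protocol, which is not shown.
- *A false-positive rate of 13% to 46% is to be expected.* That is the case in which therapists took every baseline, the shift favoured the intervention and change scores were tested. The share, size and direction are all unknown.
- *The 12-month change compares a therapist's meeting with a mailed form.* That is one permitted combination; meetings with project staff are allowed at both times. The article also disclaims firm long-term evidence.
- *Condition is known before baseline.* The Assessment section says "Before being allocated to one of the two study conditions, participants have to complete the baseline measurement", while the Allocation section says "the vast majority of the control group participants are recruited from the support groups’ own waiting lists". Whether the stated order holds in practice is a separate allocation question and is no part of this point.

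The asymmetry in who may collect the baseline remains after all of these. The article itself fixes it and does not list it as a limitation.

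**Conclusion.** The point holds in a limited form. The plan allows a therapist to collect some intervention baselines and provides for this in no control child, so a collector effect can enter that arm's baseline. It would then affect the baseline comparison of the arms, the within-group changes including the one at 12 months, and any between-group analysis that uses baseline. Its direction and size cannot be derived from the document. Under the assumptions in steps 4 and 5, the false-positive rate runs from 6.5% to 45.6%, or 8.2% to 19.0% if therapists took half the baselines; the opposite direction costs power. These figures illustrate sensitivity and do not estimate the bias. The matter is worth correcting because the remedy is cheap; it does not invalidate the design.

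**What to change.** In the Assessment section, for all remaining assessments:

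1. Use one procedure in both arms: project staff hand out and collect the forms. Where a therapist hosts the meeting, the child and parent complete the forms privately and seal them for return to project staff, without the therapist helping or seeing the answers.
2. Record collector and mode for every form, retrospectively where this can be established.
3. Add a sensitivity analysis restricted to, or adjusted for, baselines collected by project staff.
4. Name the asymmetry under Strengths and limitations. Recruitment has run since March 2010, so baselines already taken cannot be repeated.

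The cost is slightly more scheduling, two data fields, one extra analysis and a supply of envelopes. The prepaid envelope in the Recruitment section is for consent forms, so envelopes for questionnaires are an addition. If the full protocol already requires private, sealed completion, items 2 to 4 are enough.

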### Outcome measurements

#### Primary outcomes

To measure overall mental health, the Swedish version of a three-point likert scales, the Strength and Difficulties Questionnaire (SDQ; [35,36]) (SDQ-swe) is used. The SDQ-swe P4-16 version is to be filled out by the parent(s) of those children who are 7–10 year olds while the SDQ-swe S11-16 is a self-completion scale for those children who are 11–13 years old. The original SDQ and the Swedish version have been demonstrated to be reliable and valid among samples of 11–16 and 6–10 year olds, respectively [36,37].

Overall life satisfaction and future hope is measured by asking the children about their past, present- and future life rating, on a ten-point “Ladder of life” which represents life status from “worst” to “best” possible life imaginable [38-40]. The original version [38] was designed for adults and asked the respondents to consider a five-year perspective. A modified version asks children to rate their life satisfaction using a shorter time-frame of one year [39] and is used in this study for all children.

Self-perception and self-esteem is measured using the Swedish scale “Jag tycker jag är” [I think I am] [41] and is scored by the children themselves. This scale has previously been demonstrated to be reliable among Swedish university students [41,42].

Emotional climate and personal interaction within the family is measured using the Swedish scale “Familjeklimat” [Family Climate] (Hansson 1989) and is scored by the parents. This instrument consists of 85 adjectives which can be subdivided into four dimensions: “closeness” pertains to adjectives describing a positive climate with warmth, safety and harmony; “distance” comprise adjectives describing a negative atmosphere governed by coolness and rejection; “spontaneity” relates to adjectives describing the family’s emotional expressiveness in both positive and less positive terms; “chaos” pertains to adjectives that relates to a state of disorder within the family.

Coping behaviour is measured using three-point likert scales, the Kids Coping Scale (KCS; [43]), which has been translated into Swedish for the purpose of this study. This scale has demonstrated low to moderate levels of internal consistency and validity among a cross-sectional sample of 7–13 year olds [43] and is to be filled out by the children themselves.

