### Sample size

This trial is designed to detect a medium or larger effect size corresponding to a standardized mean difference of Cohen’s d >0.5 [46]. Our hypothesis is directional in favour of the intervention. Based on differences between means, an *a priori* calculation of the estimated sample size, using the G*Power software [47] where an allocation ratio of 1.8 has been set, reveals that it is required that a minimum of 116 participants (75 in the intervention group and 41 in the control group) enrol in the trial (power = 0.80, α = 0.05, one tailed).

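### Five unranked primary outcomes are set against a sample size for one unadjusted test; if any one may carry the claim, the false-positive risk is about 13.5% to 22.6%, not 5%

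*Protocol article*

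**What the plan says.** Under Primary outcomes, the protocol article places five instruments and singles out none:

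- the SDQ, completed by parents of children aged 7–10 and by the children themselves at ages 11–13;
- the Ladder of life: "Overall life satisfaction and future hope is measured by asking the children about their past, present- and future life rating", in a version with a one-year time frame;
- Jag tycker jag är, for self-perception and self-esteem;
- Family Climate, scored by parents: "This instrument consists of 85 adjectives which can be subdivided into four dimensions";
- the Kids Coping Scale.

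The only other outcome listed is adherence, which therapists report. Every effect measure is therefore primary.

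The Sample size section gives one calculation: "This trial is designed to detect a medium or larger effect size corresponding to a standardized mean difference", with "standardized mean difference of Cohen’s d >0.5", "an allocation ratio of 1.8 has been set" and "power = 0.80, α = 0.05, one tailed". It arrives at 116 children, 75 in the intervention group and 41 in the control group, and does not name the outcome. The Analyses section compares means on the outcome measurements between and within groups. It does not rank the outcomes or say which result would decide the question.

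**The concern.** Two things the article fixes do not fit together. It designates five primary outcomes, and it sizes the study for one test at the full one-sided 5%. The hypothesis at the end of the Background is only that the groups will have positive effects, which a good result on any one scale could be said to meet. A reader of the final report could then see effectiveness claimed on whichever instrument crossed the threshold, with a false-positive risk well above the single level stated. If the five were adjusted for instead, 116 children would no longer give the stated power for each of them.

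**Working it through.** **Inputs from the Sample size section.** d = 0.5, one-sided α = 0.05, power 0.80, allocation ratio 1.8, groups of 75 and 41. **From Primary outcomes:** five instruments. **Assumed, because the article gives no figure:** a common correlation r between the test statistics, from 0 to 0.7.

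**1. Reproducing the stated sample size.** For a one-sided two-sample t-test the noncentrality is d·√(n₁n₂/(n₁+n₂)).

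- With 75 and 41: 0.5·√(75·41/116) = 2.574. With 114 degrees of freedom the critical value is 1.658, so power is 0.82.
- The smallest t-test design at ratio 1.8 is 71 + 39 = 110, with power 0.802.
- Allowing for a Wilcoxon–Mann–Whitney test (efficiency 3/π) gives 74 + 41 = 115, and power 0.804 at 75 and 41.

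The stated 116 therefore matches one one-sided test at 0.05. It is slightly conservative for a t-test and is not an error.

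**2. Chance of at least one false positive over m tests, each at one-sided 0.05.**

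- Independent tests: 1 − 0.95^m. For m = 5: 1 − 0.95⁵ = 0.226.
- Equal correlation r, with c = 1.645: 1 − ∫ φ(x)·Φ((c − √r·x)/√(1 − r))^m dx.

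| r (assumed) | m = 5 | multiple of 5% | m = 10 | multiple of 5% |
|---|---|---|---|---|
| 0 | 22.6% | 4.5 | 40.1% | 8.0 |
| 0.3 | 19.3% | 3.9 | 30.7% | 6.1 |
| 0.5 | 16.6% | 3.3 | 24.7% | 4.9 |
| 0.7 | 13.5% | 2.7 | 18.5% | 3.7 |

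The m = 10 columns are a scenario only. They count each Ladder rating and each Family Climate dimension as a separate test: 1 + 3 + 1 + 4 + 1 = 10.

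**3. Power if α is split over five outcomes.** Each test then has α = 0.05/5 = 0.01. At 75 and 41 the noncentrality is still 2.574, the critical value rises to 2.360, and power per outcome is 0.586. Restoring 80% per outcome by t-test would take 116 + 64 = 180 children.

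**4. Power if all five must succeed.** There is no inflation under this rule. With d = 0.5 on every outcome, joint power is 0.82⁵ = 0.37 if the outcomes are independent and 0.55 at r = 0.5. The 80% does not describe this reading either.

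**The case against.** Four points can be made for the plan.

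*No success rule is stated.* The inflation needs an any-one-suffices rule, and the article does not give one. The objective lists separate research questions on mental health, coping and quality of life. If each is reported only as its own question, each test keeps its 5% and a generic d = 0.5 calculation can serve each in turn. This stands, and it makes the error figures conditional. It does not settle the matter, because the objective is one overall question of effectiveness and all five instruments are labelled primary for it.

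*The multiplicity procedure may sit in an analysis plan that is not shown.* This also stands, and the absence of a procedure is not the finding. The finding is the mismatch between five primaries and a one-test sample size. An adjustment made elsewhere would reduce the power at 116 children.

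*The level is stated only for planning.* One-sided 0.05 appears in the Sample size section and is not repeated under Analyses. Applying it to every test is an inference, although it is the only level given.

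*Ten scores and an eightfold risk.* A reader might infer these from the Ladder and Family Climate descriptions. The article says that Family Climate can be divided into four dimensions and that the Ladder has three ratings. It does not say that each is tested separately. Eightfold would also need ten independent tests, which is implausible for ratings on one ladder and dimensions of one adjective list. Five is the documented count.

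A reader might also infer that the SDQ must be the single primary because it is listed first and has cited reliability. The article does not support that. The SDQ combines parent report at 7–10 with self-report at 11–13, and the Kids Coping Scale also has cited evidence at 7–13, though weak: "This scale has demonstrated low to moderate levels of internal consistency and validity".

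**Conclusion.** The concern holds in a conditional form. Five unranked primaries stand against a sample size for one comparison with no named outcome. If one significant primary is enough and each is tested at one-sided 0.05, the chance of at least one false positive is 13.5% (r = 0.7) to 22.6% (r = 0), or 2.7 to 4.5 times 5%. If all ten scores were tested, which the article does not state, it would be about 19% to 40%. The correlations are assumed throughout. The stated 80% is sound for a single unadjusted test (0.82 at 75 and 41). With Bonferroni over five it is about 0.59 per outcome.

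**What to change.** Make one of two changes, dated and before outcome data are analysed. Recruitment has been under way since March 2010, so the timing relative to data access should be recorded.

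1. **One primary outcome.** Name one outcome at four months, the only follow-up that allows a between-group comparison. Tie the power statement to it. Make the other instruments secondary, tested with Holm or labelled exploratory. The choice belongs to the investigators. If it is the SDQ, state how the parent and self-report forms are combined. If it is Jag tycker jag är, note that the reliability evidence cited comes from an older group: "This scale has previously been demonstrated to be reliable among Swedish university students".
2. **Five primary outcomes.** Test them with Holm, with one score defined per instrument, and restate the power as about 0.59 per outcome at the strictest step.

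Under either option, do not use the past Ladder rating as an effect measure if its one-year frame refers to a time before the intervention. If it means one year ago, the four-month rating would refer to 12 − 4 = 8 months before baseline.

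The cost is protocol wording and a registry update, with no new participants or data. The downside is that under option 1 the demoted scales can no longer carry the effectiveness claim alone, and under option 2 the stated power becomes less favourable.
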